## Abstract

**Background:**

Behavioural problems are common in early childhood, and can result in enduring costs to the individual and society, including an increased risk of mental and physical illness, criminality, educational failure and drug and alcohol misuse. Most previous research has examined the impact of interventions targeting older children when difficulties are more established and harder to change, and have rarely included fathers. We are conducting a trial of a psychological intervention delivered to families with very young children, engaging both parents where possible.

**Methods:**

This study is a two-arm, parallel group, researcher-blind, randomized controlled trial, to test the clinical effectiveness and cost-effectiveness of a parenting intervention, Video Feedback Intervention to Promote Positive Parenting and Sensitive Discipline (VIPP-SD) for parents of young children (12–36 months) at risk of behavioural difficulties. VIPP-SD is an evidence-based parenting intervention developed at Leiden University in the Netherlands which uses a video-feedback approach to support parents, particularly by enhancing parental sensitivity and sensitive discipline in caring for children.

The trial will involve 300 families, who will be randomly allocated into either an intervention group, who will receive the video-feedback intervention (n = 150), or a control group, who will receive treatment as usual (n = 150). The trial will evaluate whether VIPP-SD, compared to treatment as usual, leads to lower levels of behavioural problems in young children who are at high risk of developing these difficulties. Assessments will be conducted at baseline, and 5 and 24 months post-randomization. The primary outcome measure is a modified version of the Preschool Parental Account of Child Symptoms (Pre-PACS), a structured clinical interview of behavioural symptoms. Secondary outcomes include caregiver-reported behavioural difficulties, parenting behaviours, parental sensitivity, parental mood and anxiety and parental relationship adjustment. An economic evaluation will also be carried out to assess the cost-effectiveness of the intervention compared to treatment as usual.

**Discussion:**

If shown to be effective, the intervention could be delivered widely to parents and caregivers of young children at risk of behavioural problems as part of community based services.

**Trial registration:**

ISRCTN Registry: ISRCTN58327365. Registered 19 March 2015.

**Electronic supplementary material:**

The online version of this article (doi:10.1186/s13063-017-2293-9) contains supplementary material, which is available to authorized users.

## Background

Behavioural problems affect 5–10% of children, and children with established behavioural problems are at risk of significantly worse outcomes through childhood and into adult life [1, 2]. They are more likely to experience psychiatric disorders, antisocial behaviour and criminality, drug and alcohol misuse, educational failure and physical ill health [1, 3–8]. Therefore, behavioural problems can lead to high levels of difficulties and unhappiness for young people and their families, and large costs to society through the health, social care and criminal justice systems.

A key risk factor for the development of behavioural problems is the quality of the parental care that children receive. In particular, low levels of sensitive parenting and greater use of harsh discipline have been causally linked to the development of behavioural problems [7]. Reviews demonstrate that interventions that begin in the first years of life offer a viable means of promoting parenting skills and optimising developmental trajectories for children [9–12]. In addition, strong evidence also indicates the increased opportunities and cost return achieved when interventions begin early in the life course [13–15].

Some key early interventions for behavioural problems have been identified [11, 12], including those which show potential for delivery on a wide scale. For example, home visiting [16] is now being used across the United Kingdom and shows promise, but it is focused on a limited target group, and requires intensive professional input over a long period of time and a broad developmental remit. As the Harvard Policy Review [17] points out: “No single program approach or mode of service delivery has been shown to be a magic bullet”. Thus, rigorous evidence is needed to identify complementary and alternative approaches. In particular further research is needed regarding brief programmes that are effective in promoting positive interactions between infants and both mothers and fathers [18], as including two caregivers in interventions may lead to increased efficacy [9, 19, 20].

Video Feedback Intervention to Promote Positive Parenting and Sensitive Discipline (VIPP-SD) may offer a compelling means of promoting behavioural outcomes, given its strong theoretical underpinnings and burgeoning evidence base [21–23]. The VIPP-SD intervention is derived from the principles of both attachment [24] and social learning/coercion theory [25–27]. From an attachment perspective the promotion of sensitive parenting improves the relationship that children have with their primary caregiver, while social learning/coercion theory suggests that child externalising problems are more likely to emerge when a child is reinforced for responding with negative behaviour to parental requests or demands [24–27]. VIPP-SD consists of six sessions, which use video-recorded clips of parents’ interactions with their child to improve sensitivity by enhancing the parent’s capacity to identify the child’s exploratory behaviour and attachment cues and to respond to them appropriately [28]. Each session also incorporates aspects of social learning theory through an explicit focus on parental discipline strategies [26], to increase positive and reduce aversive interactions. Overall, the intervention represents a powerful combination of the insights from the attachment and social learning perspectives [29].

The VIPP intervention has been tested in 11 randomized controlled trials in different settings and with different groups of families. It has an evidence base for early preventive intervention with effects shown on parental sensitivity in parent-child interactions, positive parental discipline practices and child behaviour [21–23, 30–37]. Preliminary evidence also supports its feasibility with and acceptability amongst fathers [38]. Although this evidence is encouraging, VIPP-SD has yet to be tested in the United Kingdom for children with behavioural problems. In addition, targeted studies are needed to provide specific evidence of its cost-effectiveness above and beyond standard care.

## Methods/design

### Study aim

To evaluate the effectiveness and cost-effectiveness of a brief early parenting intervention, designed to prevent enduring behavioural problems in high risk young children aged 12–36 months old.

### Primary hypothesis

Among children with high levels of behavioural problems aged 12–36 months, adding a brief video-feedback parenting intervention (VIPP-SD) to treatment as usual will reduce enduring behavioural problems measured at 5 months post-randomization, using the Preschool Parental Account of Child Symptoms (Pre-PACS) interview.

### Secondary hypotheses

i.Among children with high levels of behavioural problems aged 12–36 months, adding a brief video-feedback parenting intervention (VIPP-SD) to treatment as usual will reduce enduring behavioural problems measured at 2 years post-randomization, using the Pre-PACS interview.ii.Among children with high levels of behavioural problems aged 12–36 months, adding a brief video-feedback parenting intervention (VIPP-SD) to treatment as usual will reduce enduring behavioural problems measured at 5 months and 2 years post-randomization, using the Child Behavior Checklist (CBCL) and the Strengths and Difficulties Questionnaire (SDQ), completed by parents/caregivers and the SDQ completed by a nursery practitioner/teacher.iii.Among children with high levels of behavioural problems aged 12–36 months, adding a brief video-feedback parenting intervention (VIPP-SD) to treatment as usual will lead to improved parent-child interactions (improved parental sensitivity and engagement) measured at 5 months.iv.Among children with high levels of behavioural problems aged 12–36 months, adding a brief video-feedback parenting intervention (VIPP-SD) to treatment as usual will provide a more cost-effective use of resources.

### Design

The study is a two-arm, parallel group, researcher-blind, randomized controlled trial (RCT), to test the clinical and cost effectiveness of VIPP-SD for parents of young children (12–36 months) at risk of behavioural difficulties. The trial will involve 300 families, who will be randomly allocated into either the intervention, receiving VIPP-SD in addition to treatment as usual (n =150) or the control group, receiving treatment as usual alone (n = 150). Assessments are undertaken at baseline and 5 and 24 months post-randomization. Figure 1 shows the projected participant flow through the trial.

**Fig. 1 Fig1:**
[figure not shown]
CONSORT diagram of projected participant flow through the trial

### Participants and eligibility

Intervention is provided in the community through local health practitioners. Participants are children aged 12–36 months who demonstrate emerging behavioural difficulties and their parents. To be eligible to participate families must meet the following inclusion criteria and none of the following exclusion criteria:

Inclusion criteria:Parents aged ≥ 18 years;Child aged between 12 and 36 months;Child scores in the top 20% for behavioural problems on the SDQ;Written informed parental consent from participating parents.

Exclusion criteria:Child or parent has severe sensory impairment, learning disability, or language limitation, which is sufficient to preclude participation in the trial.Siblings participating in the trialFamilies participating in active family court proceedingsParent/carer is participating in another closely related research trial and/or is currently receiving an individual video-feedback-based intervention.

### Recruitment

Participants are recruited predominantly through UK National Health Service (NHS) sites, via health visiting services, child and adolescent mental health services, GP services, and through links with children’s centres and other community services. At the time of writing there are four sites - London Boroughs of Camden, Islington, and Hillingdon, as well as Oxfordshire, with three further additional sites anticipated. There are two study phases. Phase 1 involves screening to identify those families who fall into the top 20% for behavioural difficulties on the Strengths and Difficulties Questionnaire. Phase 2 involves random assignment to the intervention or treatment as usual. The study conforms to the SPIRIT guidelines, and a SPIRIT figure and checklist are provided (Additional file 1 and Fig. 2).

**Fig. 2 Fig2:**
[figure not shown]
Spirit figure

#### Phase 1

Parents are recruited into the study using a number of strategies. The principal recruitment pathway is through health visiting services. Health visitors recruit families to take part in the study using a screening pack at routine 12 and 24 month health reviews. This is augmented by direct recruitment by the study team and clinical research network support staff in the waiting room at health visiting reviews/clinics as well as through mailshots of the screening pack and/or study advertisements using health visiting databases. Families are also recruited through other clinical and community services, including GP services, child and adolescent mental health services, children’s centres, nurseries, and other community venues either through direct contact with clinicians and practitioners using the screening pack or by signposting families to poster advertisements. Information is also provided through social media as well as advertisements in community media outlets.

The screening pack includes an invitation letter, an information sheet, a consent form regarding participation in Phase 1 of the study, and the screening questionnaire which comprises the SDQ, and a small number of demographic variables including caregiving status, age, and educational attainment. Participants can return hard copies of the screening questionnaire and consent form included in the screening pack directly to the clinician/practitioner or researcher/member of the clinical research network support staff or return via a freepost envelope provided. Alternatively, participants can complete the same forms electronically via the study website. Those caregivers whose children meet eligibility criteria based on their SDQ scores (top 20% using population norms) are then contacted by a member of the research team via telephone to determine the family’s full eligibility and interest in the trial phase of the study. Families who are both eligible and interested in participating in the full study progress to phase 2.

#### Phase 2

Those participants who are interested in participating in the full study are provided with an information pack for phase 2 and a date is arranged to meet with them in order to conduct the first assessment visit where appropriate. Participants are randomized following this visit.

### Randomization

Site-level randomization lists are prepared by a statistician using 1:1 allocation and appropriate block sizes and uploaded on to the study electronic data capture system. Eligible subjects are allocated online to the next available treatment code in the appropriate randomization list. Randomization is stratified by recruitment site and by willingness and availability of both parents to be involved, versus one only.

### Intervention

VIPP-SD is a manualised, home-based intervention, delivered over six sessions at approximately fortnightly intervals. Each session involves two parts, the first part involves filming parent-child interactions and the second part involves giving parents focused feedback based on the filmed interactions from the previous session.

The intervention is delivered by trained, supervised health practitioners, predominantly health visitors. They deliver the intervention in participants’ homes (or another location according to participant preference). The key role of the therapists is to develop a trusting relationship with the participants in the treatment arm, and to deliver the treatment in six sessions in accordance with the manual. Treatment is monitored closely for fidelity to the manual by the clinical supervisor. Therapists also provide subjective ratings of fidelity for each session. All sessions are audio-recorded and a random proportion of sessions will be assessed by an independent researcher trained in the intervention. The six treatment sessions comprise of:Four core sessions: these aim to enhance the parent’s capacity to identify the child’s exploratory behaviour and attachment cues and to respond to them appropriately, and to support parents in responding consistently and sensitively to challenging behaviours;Two booster sessions: these are spaced one month apart, and the key messages are repeated using continuing video interaction material at each session.

### Treatment as usual

Participants in both groups will continue to receive treatment as usual. This may include a range of services such as health visitor services, GP advice, early intervention mental health services linked to children’s centres, and parenting advice and support sessions. Data on concurrent use of health services is collected including number of sessions offered, where they were provided, and which healthcare (or other non-healthcare) professionals/practitioners provided the care.

### Measures

Outcome measures are collected during assessment visits conducted by researchers blind to the family’s treatment status. Assessments are conducted at baseline/pre-randomization, and at 5 and 24 months post-randomization. The baseline assessment includes a brief demographic interview. All researchers conducting the assessment visits and collecting trial data at baseline, 5 months and 24 months, are blinded to participants’ allocation.

### Primary endpoint

The primary outcome is an assessment of severity of behavioural problems using a modified version of the Preschool Parental Account of Child Symptoms (Pre-PACS), a semi-structured investigator-led interview administered to a parent or caregiver. The modification of the Pre-PACS for this study was carried out in collaboration with one of its developers through piloting and discussion and all researchers conducting assessments received extensive training on administering the interview. The main revisions were made to facilitate its extension in measuring the attention deficit hyperactivity disorder (ADHD) and conduct symptoms in younger children aged between 12 and 30 months old. The interview has previously been validated for preschool-aged children.

To determine Pre-PACS scores, the primary caregiver is asked to recall and describe detailed examples of the child’s typical behaviour over the last week in a range of settings (e.g. in the home, with friends, in public). The caregiver is also asked how representative the behaviour is of the last 4 months (to ensure the example is typical and characteristic of the child). The interviewer then rates the severity and frequency of the symptoms on the basis of their professional/clinical judgement and written definitions and thresholds of the behaviours. Symptoms are rated for frequency and severity on two subscales, one measuring ADHD/hyperkinesis and the other measuring conduct problems and antisocial behaviours.

The Pre-PACS has high inter-rater reliability and good construct validity, and has been used in previous clinical trials (e.g. [39–42]). Semi-structured interviews are the gold-standard measure for most psychiatric disorders. They are more objective as they use investigator-based criteria for scoring symptoms, and are thus less prone to parental biases, which are seen when using parent-reported questionnaires. Interviews are recorded for reliability purposes and are assessed periodically to avoid drift and to ensure that the measure remains robust to rater and respondent bias.

### Secondary endpoints and demographic measures

Child behaviour is also measured using parent reports on the Child Behavior Checklist [43], which is a robust and widely used questionnaire, yielding a total behaviour score and scores for children’s internalising and externalising difficulties. The latter comprises syndrome scores for attention problems and aggressive behaviours. The measure includes 100 items each relating to a specific behaviour where caregivers are asked to indicate whether the behaviour is *not true, somewhat/sometimes true,* or *very/often true* of the child in the reference period between *now or within the past 2 months.* The CBCL was designed for use with children aged 1 ½ to 5 years old, and has since been validated for use with children aged 12 months [44].

In addition parents and nursery practitioners/teachers will complete the Strengths and Difficulties Questionnaire (SDQ) [45], a brief and widely used measure of child behaviour which assesses emotional difficulties, conduct problems, hyperactivity, peer relationship problems, and prosocial behaviour. The measure includes 25 items which require the respondent to rate how true the statement is of the child over the last 6 months (*Not true, somewhat or sometimes true, very true or often true*). SDQ scores from the conduct and hyperactivity scales will be combined to provide an overall externalising behavioural difficulties score.

Parent behaviour is assessed using the Parenting Scale [46], a reliable and valid measure of dysfunctional discipline practices in parents. Parental sensitivity will be rated based on video-recorded parent-child interactions, using a standardised rating scale, by raters blinded to group allocation. Parents’ relationship adjustment is measured using the Revised Dyadic Adjustment Scale (RDAS) [47], which generates subscale scores for consensus, satisfaction, and cohesion as well as a total adjustment score. Parental mood is measured using the widely used Patient Health Questionnaire 9 (PHQ-9) to index depression severity [48], while anxiety is measured using the Generalised Anxiety Disorder 7 (GAD-7) [49], a seven-item generalised anxiety disorder questionnaire that has been extensively used in research as a general measure of anxiety in adults. The Alcohol Use Disorders Identification Test (AUDIT-C) [50], is being used to obtain information regarding parents’ alcohol consumption as part of the demographic interview. Parents who are allocated to the intervention arm are also asked to complete a feedback questionnaire following the 5-month assessment to explore their satisfaction with and experiences of the VIPP programme. Finally, to support the economic analysis, the Child and Adolescent Service Use Schedule (CA-SUS), described below, is used to quantify service use.

### Power calculation

Based on a total sample size of 300 participants, we have estimated that potential loss to follow-up may be in the order of 20%, which leaves 120 participants per arm with follow-up data. This would allow between 80% and 90% power to detect standardised effect sizes of 0.36 and 0.42 respectively, at the 5% significance level. The analysis will be adjusted for baseline behavioural score, research centre and age of child, which will increase power, probably to over 90% for the 0.36 effect size (since such adjustment will reduce the residual error variance in our model [51]).

### Statistical analysis

Data will be analysed and presented in accordance with the Consolidated Standards of Reporting Trials (CONSORT) guidelines. The primary analysis will be by intention to treat (ITT). Descriptive analyses, including histograms and box plots, will be used to assess the distributional assumptions and to check for possible outliers. Log transformations will be applied, where appropriate, in order to render the outcomes distributions closer to the normal. Bootstrap techniques will be used if this does not achieve reasonable normality, to the extent that this may influence the properties of the regression analysis. The relationship between the outcomes and other variables will be explored graphically, using scatter plots and box plots, and descriptive data will be presented in accordance with the variable type. Prior to data analysis, missingness in the baseline variables and outcomes will be investigated to assess any risk of bias and the impact on precision of estimates for the proposed statistical methods. The primary outcome, externalising behaviour (Pre-PACS), will be analysed at follow-up using linear regression analysis, adjusting for treatment centre, parental willingness to participate (one or two parents), for infant’s baseline behaviour and for infant’s age at randomization. Sensitivity analyses modelling different assumptions for missing data will be undertaken to determine the need for supplementary multiple imputation for missing values. These analyses will account for results of any losses to follow-up insofar as they pertain to differences in measured variables (i.e. under the assumption of missing at random). This will enable us to effectively incorporate information gleaned from earlier follow-up times when the final follow-up outcome is absent. This will be done by incorporating outcomes at earlier time points into the predictive model for the multiple imputation of the outcome at 2-year follow-up. Secondary outcome variables will be analysed similarly. Categorical outcome variables will be presented by treatment group, and compared using logistic/ordered logistic regression adjusted as per the processes employed for the linear regression.

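### The primary regression and the power statement treat families as independent although several practitioners deliver VIPP-SD in one arm only; if practitioners share caseloads and differ, the standard error is understated and the stated power too high

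*Protocol article*

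**What the plan says.** The protocol article, under Intervention, states: "The intervention is delivered by trained, supervised health practitioners, predominantly health visitors". The same section describes the therapists as working with families in the treatment arm. Under Design, controls receive treatment as usual alone. Economic analysis refers to a questionnaire filled in by each health visitor who delivers the programme, so there is more than one. Nowhere does the article give the number of practitioners, the families per practitioner or an ICC.

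Under Statistical analysis, the primary outcome "will be analysed at follow-up using linear regression analysis, adjusting for treatment centre", whether one or two parents take part, the child's baseline behaviour and age. No practitioner effect or clustered standard error is named, and secondary outcomes are to be handled in the same way.

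Under Power calculation, the starting point is "Based on a total sample size of 300 participants", with 20% loss, "which leaves 120 participants per arm with follow-up data". The conclusion is "between 80% and 90% power to detect standardised effect sizes of 0.36 and 0.42 respectively". The section then expects covariate adjustment to lift power at 0.36 to probably above 90%. It mentions no design effect.

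**The concern.** This is a partially nested design. Intervention families are grouped by the practitioner who treats them; control families have no such grouping. If practitioners differ in the results they achieve, families who share one have correlated outcomes, and the mean of the intervention arm varies more than a regression with independent errors allows. Centre adjustment removes differences between sites, not differences between practitioners within a site.

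The error runs in one direction. With any positive within-centre ICC and shared caseloads, intervals are too narrow for the primary and secondary outcomes, and the planning power is optimistic. The planned sensitivity analyses concern missing data and would not show it.

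**Working it through.** **Inputs from the plan.** 300 families, 1:1 allocation and 20% loss give 300 × 0.8 / 2 = 120 per arm. The level is 5%; sidedness is not stated, but two-sided reproduces the figures. Effects are 0.36 and 0.42 SD.

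**Step 1: reproduce the stated power.** With independent families, the standard error of the difference in SD units is √(2/120) = 0.1291.

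- 0.36 / 0.1291 = 2.789; noncentral t with 238 degrees of freedom gives 79.3%.
- 0.42 / 0.1291 = 3.253; the same method gives 90.0%.

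The normal approximation gives 79.6% and 90.2%. The stated 80% and 90% are therefore right on their own inputs, and those inputs contain no allowance for clustering.

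**Step 2: add one-arm clustering.** The following are assumptions, because the article gives no values: m = 4 to 10 analysed families per practitioner (120/4 = 30 down to 120/10 = 12 practitioners), within-centre ICC 0.02 to 0.10, and equal total variance in the two arms.

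- Design effect in the VIPP-SD arm: DE = 1 + (m − 1) × ICC
- Variance of the difference: DE/120 + 1/120
- True over naive standard error: f = √((DE + 1)/2)
- Type I error of the naive test: 2 × [1 − Φ(1.96/f)]
- Power of a valid test: noncentral t as above, noncentrality divided by f

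Middle case (m = 6, ICC 0.05): DE = 1 + 5 × 0.05 = 1.25; f = √(2.25/2) = 1.061; 1.96/1.061 = 1.848, so the type I error is 6.5%; 2.789/1.061 = 2.629, so power is 74.5%.

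| m | ICC | DE | f | Naive SE too small by (1 − 1/f) | Type I error | Unadjusted power at 0.36 |
|---|---|---|---|---|---|---|
| 4 | 0.02 | 1.06 | 1.015 | 1.5% | 5.3% | 78% |
| 6 | 0.05 | 1.25 | 1.061 | 6% | 6.5% | 74.5% |
| 10 | 0.10 | 1.90 | 1.204 | 17% | 10.4% | 64% |

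At the upper end, the true standard error is 20% larger than the naive one, which makes the naive one 17% too small. Below this range the effect is negligible: with ICC 0.01 and 30 practitioners, f = 1.007 and less than one percentage point of power is lost. With ICC 0, or one family per practitioner, nothing changes.

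**Step 3: the planned adjusted analysis.** The analysis is covariate-adjusted, so the unadjusted 79% is not the right baseline for judging what the trial will deliver. The article gives no covariate-outcome correlation. Assume r = 0.5, with the ICC on the residual scale. The residual SD is √(1 − 0.25) = 0.866, and the noncentrality under independence is 2.789/0.866 = 3.220.

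- Independence: 89%
- Middle case: 3.220/1.061 = 3.036, power 86% (82% if r = 0.4, 91% if r = 0.6)
- m = 10, ICC 0.05: DE 1.45, f = 1.107, power 83%
- m = 10, ICC 0.10: 3.220/1.204 = 2.674, power 76%

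Even under independence, reaching 90% at 0.36 SD needs r of about 0.51.

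**The case against.** The strongest reply is that no consequence can be demonstrated. The article gives no ICC and no caseload. The treatment is manualised, limited to six sessions, supervised and monitored for fidelity. Outcomes are assessed by blinded researchers, and centre is already in the model. All of this points to a small within-centre practitioner variance, though it does not make it zero. This part stands: the figures above are a range over assumptions, and the upper corner should not be read as equally likely.

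It can also be said that the analysis plan is not shown and may add a practitioner term or robust errors. That is possible, but the article names the model and its covariates, and its power figures reproduce without any clustering. Independence is therefore what the document states, not merely a detail left for later.

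A reader might infer three stronger conclusions that the documents do not support:

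- *That the type I error certainly exceeds 5%.* If VIPP-SD had no effect on any family, whoever delivered it, treatment would create no practitioner correlation and the test would keep its level. Inflation requires practitioner effects that vary around a mean of zero.
- *That the trial falls short of 80% power at 0.36 SD.* This applies the loss to the unadjusted 79%. With adjustment at r = 0.5, only the extreme corner of the assumed range drops below 80%.
- *That the economic results inherit the fault through resampling.* Economic analysis names acceptability curves but no bootstrap, and the bootstrap under Statistical analysis is offered only for non-normal outcomes.

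**Conclusion.** The point holds conditionally. The design is nested in one arm, and both the stated model and the stated power ignore this. Whenever the within-centre practitioner ICC is above zero and practitioners treat more than one family, the standard error is understated and the stated power too high.

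The size is not known. Under the assumed ranges it runs from trivial to material, with a middle case of a standard error 6% larger and adjusted power 3 percentage points lower (89% to 86%). The expectation of more than 90% power at 0.36 SD is weakened, while 80% is plausibly still met. These adjusted figures also rest on r = 0.5, which the article does not give. The severity is that of a recommended improvement, below an essential correction.

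**What to change.** Keep the covariates and analyse the primary and secondary outcomes with a partially nested mixed model: a practitioner random effect in the VIPP-SD arm only (each control family its own unit), a separate residual variance for each arm, and small-sample degrees of freedom because practitioners may be few. Make this the primary analysis, or at least a prespecified sensitivity analysis. State the expected number of practitioners, and restate the power over a stated range of practitioner numbers and ICC, with the assumed covariate-outcome correlation.

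The cost is small: a change of wording and one variable, practitioner identity, which should be recoverable because intervention contacts are taken from health visitor records. Intervals become slightly wider and the stated power slightly lower. No extra families are needed.
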